### Outcome Measures

#### Trial Feasibility and Acceptability-Related Outcomes

To address objectives 1a, 1b, 1c, 2a, and 2d, we will collect data on the following to assess the feasibility of a trial and acceptability of the intervention:

Number of employers registering interest in participating in the studyNumber of employers consenting to take part in the study (minimum of 8 organizations recruited within a 6-month period)Number of line managers sent information about the studyRecruitment of line managers into the study in both the intervention and control arms, and retention of those recruited through the follow-up points to completion in the intervention and control arms (70% at 3 months and 50% at 6 months)Recruitment and retention of line managers’ direct reportsLine manager views on the acceptability, usability, and utility of the intervention through postmodule feedback forms and end-of-study interviewsStakeholders’ views on the acceptability, usability, and utility of the intervention through interviewsPossible barriers and facilitators to the intervention implementation and effectiveness through interviews with line managers and stakeholders.

#### Research-Related Primary and Secondary Outcomes

In relation to objectives 2b, 2c, and 3a, we will collect the following data to assess the potential for improving line manager and direct report outcomes and inform the planning of a larger trial. The primary outcome we will assess is line managers’ confidence in creating a mentally healthy workplace [11,22,31]. The secondary outcomes will be line managers’ mental health knowledge [23]; line managers’ workplace mental health literacy [24]; line managers’ self-rating of behavior (Stress Management Competency Indicator Tool [SMCIT]–manager version) [13]; line managers’ psychological well-being (Warwick-Edinburgh Mental Well-Being Scale [WEMWBS]) [25]; direct reports’ psychological well-being (WEMWBS) [25]; direct reports’ rating of line manager behavior (SMCIT-employee version) [13]; direct reports’ sickness absence (organizational records); and direct reports’ productivity (self-reported).

### Data Collection Procedure in Intervention Arm

In the intervention arm, line managers will be invited to complete the digital training. Participants will be encouraged to complete the modules in succession, from introduction through to modules 1 to 5, aiming to complete a module a week. The training program should, therefore, be completed in 6 weeks. Data will be collected as per Table 2, at baseline, on completion of the MMW training (approximately 6 weeks after baseline), and at 3- and 6-month follow-up periods from baseline. Line managers’ direct reports will be invited to take part in the study to determine whether they notice any change in their line manager’s behavior or whether their own mental health outcomes are affected by the line manager training. Line managers’ direct reports will therefore be invited to complete web-based questionnaires at baseline when the line manager starts the training, and 3 and 6 months later. Where available, data will also be collected from organizational records on the sickness absence levels of employees managed by the participating line managers.

### Data Collection Procedure in Control Arm

Line managers in the organizations within the control arm will receive the intervention after a 3-month wait and will complete web-based questionnaires at baseline, just before the start of the training (3 months after baseline), and after completing the training (ie, approximately 6 months after baseline). Line managers’ direct reports will be invited to complete web-based questionnaires at baseline, 3 and 6 months later. Where available, data will also be collected from organizational records on the sickness absence levels of employees managed by the participating line managers.

### Measures for Line Managers (Intervention and Control)

The web-based questionnaire will contain the following items (Table 4). Demographics (including age, gender, number of years as a manager, and number of direct reports) were collected at baseline only.

**Table 4 table4:** Summary of assessments.

Activity or measure			Enrollment	Baseline	On completion of intervention (approximately 6 weeks after baseline; intervention arm only)	3 months post baseline	6 months after baseline
Obtain enrollment data			✓				
Provide username and password			✓				
Web-based consent				✓			
**Manager only**							
	Demographics			✓			
	Confidence to create a mentally healthy workplace			✓	✓	✓	✓
	Mental Health Knowledge			✓	✓	✓	✓
	Workplace Mental Health Literacy			✓	✓	✓	✓
	**Management Competency Indicator Tool-manager version**			✓	✓	✓	✓
		WEMWBS^a^ 14		✓	✓	✓	✓
**Direct reports only**							
	Demographics			✓			
	WEMWBS^a^ 14			✓		✓	✓
	Management Competency Indicator Tool-employee version			✓		✓	✓
	Self-reported Productivity Rating			✓		✓	✓

^a^WEMWBS: Warwick-Edinburgh Mental Well-Being Scale.

Line managers’ confidence to create a psychologically healthy workplace will be quantified by a self-report measure used previously by Gayed et al [11,22] by modifying a previously published supervisor scale [31]. This measure includes 6 workplace scenarios (eg, “creating a work environment that prevents and reduces stress within my team”), which require line managers to rate their confidence on a scale of 1 (“not very confident”) to 5 (“very confident”). The items are summed to create a composite score with a range of 6 to 30, with higher scores indicative of more in creating a mentally healthy workplace.

The mental health knowledge schedule (MAKS) [23] will be used to measure the line manager’s mental health. It is a 6-item measure consisting of 6 key areas, such as help-seeking, recognition, support, employment, treatment, and recovery. MAKS is measured on a 5-point Likert scale ranging from 1 (“strongly disagree”) to 5 (“strongly agree”). Items are summed to create a composite score ranging from 6 to 30, with higher scores indicating better knowledge of mental health.

Workplace Mental Health Literacy [24] aims to measure line managers’ workplace literacy. It consists of 16 items, 4 vignettes featuring various manifestations of mental ill health within the workplace, and parallel questions exploring 4 dimensions of mental health literacy. These items are rated on a 5-point Likert scale ranging from 1 (“very low”) to 5 (“very high”). A higher score represents better workplace health literacy (range 16-80).

The SMCIT [13] measures management competencies surrounding the prevention and management of work-related stress. This measure consists of 36 items examining 4 key competencies: “managing emotions and having integrity,” “managing and communicating existing and future work,” “managing the individual within the team,” and “reasoning and managing difficult situations.” Items are measured on a scale of 1 (“strongly disagree”) to 5 (“strongly agree”). Each subscale is summed together, with higher scores indicating higher levels of competency. The measure has a version for both line managers (manager version) and employees (employee version), with the same content adjusted to suit the audience.

The WEMWBS [25] aims to quantify both line managers’ and employees’ psychological well-being over time. This measure consists of 14 items asking participants to rate a series of statements (eg, “I have been feeling useful”) on a scale of 1 (“none of the time”) to 5 (“all the time”). Summed scores range from 14 to 70 with higher scores representing better mental well-being.

After each of the training modules has been completed, participating managers will also be asked to complete a web-based feedback form, giving quantitative and qualitative feedback on the module. This will include questions on fidelity delivery and engagement with the training module [29]; questions on implementation qualities [29]; and open questions about how long the module took them to complete, which aspects of the module they found most useful, what they plan to change in their managerial practice, and how the module could be improved.

### Measures for Direct Reports (Intervention and Control)

#### Overview

On registering for the training, all participating line managers in both the intervention and control arms will be asked to send an invitation to participate in a web-based survey to their direct reports. The purpose of this is to assess whether completion of the training by line managers affects their direct reports’ perception of line managers’ behavior or the mental health and sickness absence outcomes of direct reports. The web-based survey for direct reports will contain the following items: demographics (age, gender, and number of years in the organization) collected at baseline only, WEMWBS 14-item [25], SMCIT-employee version [13], and a single-item self-reported productivity rating.

The web-based survey for direct reports at follow-up will contain the same items (as above) with the addition of open-response questions about any changes to how they are managed or their line manager’s behavior.

#### Organizational Sickness Absence Records

We will collect information from the organizations regarding the sickness absence records of those the participating line managers directly manage. Preintervention data will cover the 6 months before the intervention starts. Postintervention data will cover the 6 months after intervention completion. All organizational absence records will be anonymized at source before being securely transferred to the research team.

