#### The MMW Training Intervention

The intervention is a digital, interactive training course delivered on the internet that includes evidence-based material, guidance, and practical exercises. It will be made accessible to participants through a secure website using a personal computer, laptop, tablet, or mobile phone. Although larger screen devices (eg, personal computer or standard laptop) are recommended to maximize readability. Individual usernames and passwords will be provided to each participating line manager to gain access to the training. The training materials are presented using a web-based, interactive, and multimedia software called Xerte [30]. The training material includes evidence-based guidance, interactive tasks with opportunities for reflection, short videos, embedded links, and downloadable checklists (an in-depth overview of the modules, using the TiDiER [Template for Intervention Description and Replication] checklist, is described in the MMW intervention development paper) checklist [15]. The training covers 5 topic areas, presented as a series of independent, stand-alone modules:

Module 1: looking after your own mental healthModule 2: designing and managing work to promote mental well-beingModule 3: management competencies that prevent work-related stressModule 4: developing a psychologically safe workplaceModule 5: having conversations about mental health at work

Each module is designed to take between 20 and 30 minutes to complete. Participants will be permitted by their employer to complete the training within their work hours. The training is self-led, so each participant can progress through each module at their own pace and at a time that suits them. At the start of the intervention, a suggested schedule will be provided to each participant, whereby line managers are encouraged to schedule and complete 1 module per week. Reminder emails will be sent to participants on a weekly basis to encourage engagement and completion of that week’s module.

Organizations (clusters) will communicate with line managers (either all line managers or those in selected divisions, departments, or levels of seniority) about the intervention and study. Managers in the intervention arm will be invited to register for the training and start it right away. Managers in the control arm will be invited to register for the training and start it after a 3-month wait.

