### Economic Measures

We will consider the feasibility of collecting data on costs and savings from the perspective of the employer. The costs considered will be the working hours lost to complete training during working hours, and, in turn, the cost or saving of any change in sickness absence rate over the follow-up will be calculated based on the median hourly wage (£15.6 [US $19.87] per hour) [32] of employees in the United Kingdom.

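### Sickness-absence windows follow the training dates, so on the natural reading the waitlist arm has no untrained follow-up and the arms' windows are shifted by 3 months or more

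*Protocol article*

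**What the plan says.** The section on organizational sickness absence records gives one pair of windows: "Preintervention data will cover the 6 months before the intervention starts. Postintervention data will cover the 6 months after intervention completion". It falls under the heading for direct-report measures in both arms, and the control-arm data collection section confirms that controls are included: "Where available, data will also be collected from organizational records on the sickness absence levels of employees managed by the participating line managers".

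The training dates differ by arm. In the section on the MMW training intervention: "Managers in the intervention arm will be invited to register for the training and start it right away". The intervention-arm procedure puts completion at about 6 weeks after baseline. Control-arm managers "will receive the intervention after a 3-month wait", with a post-training survey at about 6 months.

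Direct reports' sickness absence is a listed secondary outcome and part of objective 2c. The Data Analysis section says the arms will be compared at follow-up against baseline. The Economic Measures section adds that "the cost or saving of any change in sickness absence rate over the follow-up will be calculated based on the median hourly wage". No section gives the control arm a separate absence window, or one counted from baseline.

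**The concern.** A waitlist design gives a randomized comparison only while the controls are still waiting, here months 0 to 3. The surveys respect this: direct reports in both arms are measured at baseline, 3 and 6 months, so the month-3 control survey is untrained. The absence windows are tied to the training instead. For controls, this places the waiting period before training, in the pre window, and starts the post window only after training has ended.

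Two things are at stake. First, a between-arm comparison of absence change would set one trained group against another, with a control reference period that is partly after baseline. Second, each window is 6 months long and the arms' windows start at different times. An outcome that varies with season can therefore change within an arm, and differ between arms, with no training effect at all. The costing may take up that change as a saving or a loss.

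**Working it through.** **Inputs from the protocol article.** Intervention training starts at month 0 and ends about 6 weeks later. Six weeks is 42 days, and 42 / (365.25/12) = 1.38 months. Control training starts at month 3. Its end is not fixed exactly, so two values are used: 3 + 1.38 = 4.38 (same duration) and 6 (the post-training survey).

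**Windows, in months from baseline.**

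| Arm | Pre | Post |
|---|---|---|
| Intervention | -6 to 0 | 1.38 to 7.38 |
| Control, ends 4.38 | -3 to 3 | 4.38 to 10.38 |
| Control, ends 6 | -3 to 3 | 6 to 12 |

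**What follows.**
- Untrained control time (months 0 to 3) inside the control post window: 0 months in either case.
- Waiting time inside the control pre window: 3 of 6 months.
- Shift between arms: 3 months for pre; for post, 4.38 - 1.38 = 3.0 or 6 - 1.38 = 4.6 months.
- Overlap between arms: 3 of 6 months for pre; for post, 7.38 - 4.38 = 3.0 or 7.38 - 6 = 1.4 of 6 months.

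**Other reading: intervention-arm dates applied to both arms.** The control post window is then 1.38 to 7.38. It holds 3 - 1.38 = 1.6 untrained months. The rest is 1.4 months of training and 3.0 after it, or 3.0 and 1.4 if training ends at month 6. The window is still mixed.

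**Possible size of the seasonal artefact.** The protocol gives no absence rate and no seasonal pattern, so this part is an assumption throughout. Take no training effect and a rate of 1 + A cos(2πs/12), where s is months from a mid-January peak. The mean over a 6-month window with midpoint s is 1 + (2A/π) cos(2πs/12). The spurious ratio is (intervention post/pre) divided by (control post/pre).

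Worked case: A = 0.20, baseline mid-November (s = -2), control training ending at 4.38.
- Intervention pre, s = -5: 0.890. Post, s = 2.38: 1.041. Change +17%.
- Control pre, s = -2: 1.064. Post, s = 5.38: 0.879. Change -17%.
- Ratio: (1.041/0.890) / (0.879/1.064) = 1.41.

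The same formula for baselines across the stated recruitment period (September 2021 to January 2022):

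| Baseline | A = 0.20, ends 4.38 | A = 0.20, ends 6 | A = 0.10, ends 4.38 | A = 0.10, ends 6 |
|---|---|---|---|---|
| mid-September | 1.21 | 1.33 | 1.10 | 1.15 |
| mid-November | 1.41 | 1.40 | 1.19 | 1.18 |
| mid-January | 1.14 | 1.03 | 1.07 | 1.02 |

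The range is 1.02 to 1.41. Rounding 6 weeks to 1.5 months moves no ratio by more than about 0.01. Under this assumed season every ratio exceeds 1, so absence would appear to develop worse in the intervention arm.

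**The case against.** The strongest reply is that the protocol never says the windows use each arm's own dates, so the problem rests on inference. That is correct as to wording. But the intervention is the only anchor given and its dates differ by arm, so this is the natural reading, and the common-dates reading still leaves a mixed control window.

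A second reply concerns the role of the outcome. This is a feasibility pilot that puts no emphasis on P values. Absence is one secondary outcome, collected where available, and part of the question is whether employers will release the records at all. The between-arm sentence in Data Analysis is general and does not name absence, and the costing is itself framed as a feasibility exercise. All of this stands and lowers the priority. It does not make the windows suitable for the comparison described.

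Third, a 6-month window after completion may be deliberate, to give managers' behavior time to change and absence time to respond. That is a fair reason to keep it as a description, but it does not provide an untrained comparator.

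A reader might go further and infer that the arms are observed in wholly different months, that the absence data are useless, or that season will certainly appear as benefit or harm. The documents do not support this. The windows overlap in part, each arm's before-after change can still be estimated, and no seasonal amplitude is given. For a mid-January baseline with control training ending at month 6, the assumed artefact almost vanishes.

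**Conclusion.** The point holds and should be fixed, at moderate weight. As worded, and on the natural reading of the dates, the control arm has 0 untrained months in its absence post window, and 3 of the 6 months in its pre window lie after baseline. The windows are offset between arms by 3 to 4.6 months. The between-arm comparison of change therefore cannot isolate a training effect on absence, and within-arm change, which may feed the costing, is open to confounding by season.

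The structural result depends only on the stated training dates and on reading the anchor as arm-specific. The ratios of 1.02 to 1.41 rest on an assumed 10% to 20% swing, a mid-January peak, no training effect, and the choice of control completion date. They illustrate scale and are not estimates.

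It would be wrong to infer that the trial's randomized comparison fails as a whole. The primary outcome and the direct-report surveys have an untrained control measurement at 3 months. Only the records-based absence outcome and its costing are affected.

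**What to change.** Request absence days and headcount by calendar month, for the teams of participating managers, from month -6 to at least month +6 counted from baseline in both arms. Make months 0 to 3 the randomized between-arm comparison, adjusted for the absence rate over the common pre-baseline window (-6 to 0). Use that comparison for any cost or saving attributed to training. Keep the training-anchored 6-month windows, labeled as descriptive, and state which dates define them in the control arm.

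The change is mainly a reworded data request. Its statistical cost is real: the randomized window is 3 months instead of 6, so rates are less precise. About 1.4 of those 3 months are training time in the intervention arm, leaving about 1.6 after completion, so any effect on absence is diluted.

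The article reports that data analysis finished in August 2023. If monthly records can no longer be obtained, the absence and costing results should be reported as descriptive before-after change in each arm, and the baseline-anchored request carried into the main trial.

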### Data Analysis

Statistical analysis will produce summary statistics to assess the parameters for a full trial. Missing data will be imputed using multiple imputations. SPSS (version 26; IBM Corp) will be used for statistical analysis. As this is a pilot trial, no emphasis will be put on the *P* values for any inferential statistical tests conducted. The primary analysis will use an intent-to-treat approach with repeated measures. Differences between the intervention and waiting list control groups at follow-up will be examined against baseline. The pilot data will provide information on the parameters needed for a realistic sample size calculation (mean, SD, and treatment effects of the primary outcome for the 2 arms) for a future main cluster RCT.

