### Design

This feasibility pilot study is a multisite, 2-armed cluster RCT taking place in work organizations of different sizes and sectors across the Midlands area of England. The organizations are the units of randomization (the clusters), with data collected from individual line managers (the participants) and the direct reports who are supervised by managers within those organizations. If large, multisite organizations are recruited for the study, we will consider the option of using an internal control group within that organization if there is a low risk of contamination between the intervention arm and control arm within that large organization. The data collection schedule for the study is summarized below for the intervention arm (Table 2) and the control arm (Table 3). A repeated measures design will be adopted, whereby participating line managers in the intervention arm will complete web-based questionnaires at baseline, on completion of the MMW training (approximately 6 weeks after baseline), and at 3- and 6-month follow-up periods after baseline. A 3-month waitlist control group will be used with participating line managers. They will be asked to complete web-based questionnaires at baseline, 3-month follow-up (before starting the intervention), and after completion of the training (6 months after baseline).

**Table 2 table2:** Data collection schedule for the intervention arm.

			Baseline survey		Postintervention survey (approximately 6 weeks after baseline)		3 months after the baseline follow-up survey		6 months after the baseline follow-up survey		Process evaluation interviews

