### Sample Size

A minimum of 8 clusters (randomized into 2 groups of 4) will be sought to inform a future trial, as recommended for pilot clinical trials [26]. We will aim to recruit 30 line managers for each arm as per guidance for feasibility trials [27].

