### Allocation to Intervention

Organizations (clusters) will be randomly assigned (1:1) to either the intervention or waiting list control group using a web-based random sequence generator [28]. This allocation will be stratified to ensure a spread of different sizes of organizations within the intervention and control arms. Where the organization is sufficiently large to have distinct departments, divisions, or units with minimal risk of contamination between them, we will randomly assign 2 of these different departments, divisions, or units to either intervention or waiting list control using the same approach.

The research team and participants will not be blinded to the outcome of randomization due to practical reasons (ie, sending reminder emails to participating managers). The lead researcher will enroll participating organizations and line managers and will assign organizations (clusters) to the intervention or control arm.

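### The primary analysis names no allowance for clustering by organisation or for the size stratum, and the list of parameters for the future cluster trial omits the ICC

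*Protocol article*

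**What the plan says.** The Design section fixes the level of randomisation: "The organizations are the units of randomization (the clusters), with data collected from individual line managers". Direct reports, nested within those managers, are surveyed as well. Allocation to Intervention adds a stratification factor: "This allocation will be stratified to ensure a spread of different sizes of organizations within the intervention and control arms". It also provides for large organisations with separable units: "we will randomly assign 2 of these different departments, divisions, or units to either intervention or waiting list control". This provision is conditional, and the article does not say whether any organisation was split.

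The Data Analysis section describes the analysis in one sentence: "The primary analysis will use an intent-to-treat approach with repeated measures". It then says that follow-up differences between arms will be looked at relative to baseline, that missing data will be multiply imputed in SPSS, and that P values will carry no weight. As inputs for sizing a future cluster trial it lists means, SDs and treatment effects on the primary outcome. The third objective, in the Objectives section, is to supply parameters on both sample size and clustering.

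**The concern.** Managers in one organisation share policies, workload, senior support and a gatekeeper, so their scores are likely to be correlated. Repeated measures handles correlation within a person over time. It does not handle correlation between people in the same randomised organisation. A model that stops at the person treats managers as independently allocated and gives too small a standard error for the arm difference whenever the ICC is above zero.

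Two things are at stake. One is the apparent precision of the treatment effect, which the article intends to carry into the main-trial sample size. The other is the ICC itself: a cluster trial cannot be sized from a mean, an SD and an effect alone, and the pilot's own objective promises information on clustering.

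**Working it through.** **Inputs from the article.** Recruited: 224 managers in 24 organisations (Results). Planned minimum: 8 clusters, with 30 managers per arm (Sample Size). Retention criterion: 70% of managers at 3 months (Trial Feasibility and Acceptability-Related Outcomes).

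**Assumption.** No ICC is given, so a range of 0.01 to 0.10 is used for the score being analysed.

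The article has no power calculation, so there is no figure of its own to reproduce. Its targets agree with each other: 2 × 4 = 8 clusters and 2 × 30 = 60 managers.

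**Formulas.** Mean cluster size m = N / k. Design effect DE = 1 + (m − 1) × ICC. True SE / naive SE = √DE. Actual coverage of a naive 95% interval = 2Φ(1.96 / √DE) − 1.

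**Mean cluster sizes.** Recruited: 224 / 24 = 9.33. With 70% retained: 156.8 / 24 = 6.53. Planned minimum: 60 / 8 = 7.5.

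**Example.** Recruited sample, ICC 0.05: DE = 1 + 8.33 × 0.05 = 1.42 and √DE = 1.19, so the naive SE is 1 / 1.19 = 84% of the true one. Coverage = 2Φ(1.96 / 1.19) − 1 = 90.0%.

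| ICC (assumed) | Recruited, m = 9.33: DE; coverage | 70% retained, m = 6.53: DE; coverage | Planned minimum, m = 7.5: DE; coverage |
|---|---|---|---|
| 0.01 | 1.08; 94.0% | 1.06; 94.4% | 1.07; 94.2% |
| 0.02 | 1.17; 93.0% | 1.11; 93.7% | 1.13; 93.5% |
| 0.05 | 1.42; 90.0% | 1.28; 91.7% | 1.33; 91.1% |
| 0.10 | 1.83; 85.2% | 1.55; 88.4% | 1.65; 87.3% |

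**Unequal cluster sizes.** DE = 1 + ((1 + CV²) × m − 1) × ICC. With an assumed CV of 0.65 and m = 9.33, DE runs from 1.12 (ICC 0.01) to 2.23 (ICC 0.10).

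**Few clusters.** The table uses the normal quantile. With cluster-level degrees of freedom, k − 2, the correct interval relative to the naive one is √DE × t(k − 2) / t(N − 2). Over the ICC range this is 1.10 to 1.43 for 24 clusters (22 df) and 1.26 to 1.57 for the minimum of 8 (6 df).

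**Parameter list against objective.** The Objectives ask for sample-size and clustering parameters. The Data Analysis list supplies only means, SDs and treatment effects, so nothing in it delivers the clustering part.

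**The case against.** The strongest reply is that the article is silent rather than wrong. Repeated measures does not exclude a mixed model with an organisation effect. The authors plainly know that they have clusters, and random effects, stratum terms and degrees of freedom usually sit in an analysis plan, which is not shown. This has force: a reader might infer that the article states an individual-level analysis, but it states no level. It does not dispose of the point, because the section also gives its own list of what the future cluster trial needs and leaves out the ICC, against a stated objective. The model and the list both omit clustering.

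Other inferences go further than the text allows:

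- A reader might infer that baseline goes unused. The section says that follow-up is compared relative to baseline; only the form of that comparison is open.
- A reader might infer that leaving out the size stratum also narrows intervals. It does not; it usually makes them somewhat conservative.
- A reader might infer that some organisations were split between arms. The provision is conditional. If it was used, treating paired departments as independent would err in the opposite direction.
- A reader might infer that the reported SDs are biased. The design effect acts on the standard error of the arm difference and shows no bias in the individual-level SD.

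It is also fair that the article promises no confidence intervals by name, that loss of coverage is slight at an ICC of 0.01 or 0.02, and that a feasibility pilot is judged mainly on recruitment, retention and acceptability.

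**Conclusion.** The point holds at moderate severity. The described primary analysis makes no stated allowance for the randomised unit or the stratification factor, and the parameter list does not serve the clustering objective.

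The loss of precision is conditional on two things: that the analysis is run as worded without a cluster term, and that the ICC is above zero. Under those conditions the standard error is too small by a factor of 1.04 to 1.35 in the recruited sample for ICCs of 0.01 to 0.10. The exact size cannot be fixed, because the article gives no ICC and no distribution of cluster sizes. Missing the ICC matters regardless of its value, since estimating it is part of the pilot's purpose. Playing down P values lessens the consequence but does not remove it, because the treatment effect and its precision still feed the next trial.

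**What to change.** State a linear mixed model for the repeated follow-up scores:

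- Fixed effects: arm, time, arm-by-time, baseline score and organisation-size stratum.
- Random intercepts: the randomised unit, and the manager for the repeated measures.
- Small-sample degrees of freedom, for example Satterthwaite.
- If any organisation was split, the department as the randomised unit and the organisation as a block.
- For direct-report outcomes, random intercepts for the randomised unit, the manager and the direct report.

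Take the between-arm contrast at 3 months. The 6-week survey exists only in the intervention arm, and by 6 months the control arm has been trained. Report the effect with a 95% confidence interval, and add the ICC with its interval to the listed parameters. That interval will probably be wide with 24 organisations, which the main-trial sample size should take into account.

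No new data are needed, and SPSS can fit the model. The cost is wider intervals and a modest re-analysis if such a model was not already used, since the article says that data analysis finished in August 2023.
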